## Abstract

**Background:**

Although it is known both patients’ and partners’ reactions to a prostate cancer diagnosis include fear, uncertainty, anxiety and depression with patients’ partners’ reactions mutually determining how they cope with and adjust to the illness, few psychosocial interventions target couples. Those that are available tend to be led by highly trained professionals, limiting their accessibility and long-term sustainability. In addition, it is recognised that patients who might benefit from conventional face-to-face psychosocial interventions do not access these, either by preference or because of geographical or mobility barriers. Self-directed interventions can overcome some of these limitations and have been shown to contribute to patient well-being. This study will examine the feasibility of a self-directed, coping skills intervention for couples affected by cancer, called *Coping-Together,* and begin to explore its potential impact on couples’ illness adjustment. The pilot version of *Coping-Together* includes a series of four booklets, a DVD, and a relaxation audio CD.

**Methods/design:**

In this double-blind, two-group, parallel, randomized controlled trial, 70 couples will be recruited within 4 months of a prostate cancer diagnosis through urology private practices and randomized to: 1) *Coping-Together* or 2) a minimal ethical care condition. Minimal ethical care condition couples will be mailed information booklets available at the Cancer Council New South Wales and a brochure for the Cancer Council Helpline. The primary outcome (anxiety) and additional secondary outcomes (distress, depression, dyadic adjustment, quality of life, illness or caregiving appraisal, self-efficacy, and dyadic and individual coping) will be assessed at baseline (before receiving study material) and 2 months post-baseline. Intention-to-treat and per protocol analysis will be conducted.

**Discussion:**

As partners’ distress rates exceed not only population norms, but also those reported by patients themselves, it is imperative that coping skills interventions target the couple as a unit and enhance both partners’ ability to overcome cancer challenges. This pilot study will examine the feasibility and potential efficacy of *Coping-Together* in optimising couples’ illness adjustment. This is one of the first feasibility studies to test this innovative coping intervention, which in turn will contribute to the larger literature advocating for psychosocial care of couples affected by prostate cancer.

**Trial registration:**

Australian New Zealand Clinical Trials Registry ACTRN12611000438954

## 

In Australia, cancer is the leading cause of disease-related burden (accounting for nearly one-fifth of the total disease burden) [1]. In 2007, 108,368 new cases of cancer were diagnosed in Australia (excluding basal and squamous cell carcinomas of the skin), and slightly more than half of these cases were men [2]. Prostate cancer is the most common type of cancer among men with 19,403 cases diagnosed in 2007 [2] and 1 in 4 men now diagnosed by 85 years of age [3]. Nearly all patients who present with localised prostate cancer will live beyond five years with the 10- and 15-year survival rates being 93% and 77%, respectively [4]. As the number of people living beyond initial diagnosis is increasing, so is the time during which the disease sequelae and psychosocial consequences must be managed. Consequently, the focus in practice and research has shifted from viewing cancer as a terminal illness to helping patients and partners learn to cope with cancer demands and optimise functioning and quality of life.

Although treatment for prostate cancer is becoming increasingly successful, the initial diagnosis still comes as a shock [5,6] and resulting treatment often adversely impacts both patients’ and partners’ quality of life, including their social, psychological, and physical functioning [5-14]. Approximately one third of men diagnosed with prostate cancer report psychological distress [15]. In some contexts, wives of men with prostate cancer have reported as much, if not more, distress than patients [5,9,16]. Although Eton et al. [9] found that men with prostate cancer and their spouses did not differ in terms of general distress; the spouses reported more cancer specific distress than the patients. The concern is that a recent meta-analysis by Hagedoorn et al.[17] found a moderate, positive association between patients’ and partners’ levels of distress (r = .29, p < .001), which implies that patient’s high distress has an impact on their partner’s illness adjustment (or vice-versa). It follows from this that psychosocial interventions should then target *couples*[18-20].

The predictors of patient and partner anxiety are typically categorised into three broad classes of variables: demographics, characteristics/stages of disease and treatment, and psychosocial [12,13,21,22]. Amongst psychosocial variables, coping is arguably one of the most frequently studied predictors of patient and partner anxiety [12,13,23]. Although findings remain equivocal, most studies support that coping strategies directed toward active engagement with the stressor, including both problem- and emotion-focused coping, are associated with more positive adjustment [24]. In contrast, those considered less functional, such as avoidance, behavioural disengagement or denial, are associated with higher levels of distress [12,13,22,25,26]. Beyond individual approaches to coping, recent studies have examined the impact of each partners’ way of coping on the other’s stress (i.e., dyadic coping) and suggest that illness adjustment is enhanced when patients and partners are mutually responsive to each other’s stress, view the cancer challenges as “our” problem or “being in it together”, and are engaged in collaborative dyadic coping by pooling their resources and problem-solving jointly [27,28]. This evidence suggests that a couple-based intervention focused on maximising use of individual and dyadic adaptive coping skills might be most promising in reducing the psychological distress of patients and partners in response to a stressful situation like cancer [21].

Recently, reviews of couple-based interventions suggest that these have the potential to be as, if not more, efficacious than patient-only interventions in optimising patient adjustment and are more efficacious than usual care in enhancing partners’ adjustment [29]. For instance, Scott et al. [30] compared the efficacy of CanCOPE (a couple-based, coping skills training intervention for women diagnosed with breast or gynaecological cancer and their partners) with an individual coping intervention and a medical information only condition. CanCOPE women reported significantly less distress and less avoidance post-intervention than the women in the other two conditions. There was also a trend for CanCOPE partners to report less distress than those in the other conditions. Similarly, Nezu et al. [31] examined the efficacy of a problem-solving therapy (PST) among a mixed sample of patients diagnosed with cancer and included two treatment groups: one in which patients attended the PST alone and another one in which PST was attended with a significant other. Post-PST positive effects on quality of life and distress were similar in the two treatment groups. However, at 6- and 12-month follow-ups, patients participating in PST with their partner reported lower distress than patients who attended the PST alone. In the context of other chronic illnesses, couple-based coping or educational interventions have also been shown to be more efficacious than individual-level interventions in optimising illness adjustment [32].

Whilst couple-based interventions are promising in enhancing couples’ illness adjustment, most are delivered by highly trained health professionals [33], limiting their long-term accessibility and sustainability, due to high cost and limited availability of qualified professionals, especially in non-metropolitan areas. In addition, it is recognised that patients who might benefit from conventional face-to-face psychosocial interventions do not access these, either by preference or because of geographical or mobility barriers [34,35]. Studies have found that as few as 14% of distressed patients with cancer accept referral to psychosocial services [36]. Thus, the challenge is to develop a cost-effective couple-based intervention that is accessible, sustainable, and efficacious. One suggestion for developing a cost-effective approach to psychosocial interventions involves using a group format instead of an individual format [37]. However, research supporting the feasibility and efficacy of group interventions over individual ones remains equivocal [37,38]. Another suggestion for cost containment is the use of a self-directed (also referred to as self-help or self-administered) format [39].

Self-directed interventions overcome some of the barriers of face-to-face services and have several potential advantages for couples, including the choice of selecting what, when, and how they want to learn. In the general self-help literature, unguided, self-help interventions, either print- or computer-based, have been shown to enhance individual well-being, including decreasing anxiety and depression symptoms [40,41]. The few self-directed, coping skills interventions developed for individuals facing cancer have been found to be acceptable [42,43], efficacious in enhancing patient well-being [39,42], particularly among distressed individuals [44], and cost-effective [39]. In a feasibility study by Alison et al. [43], when patients were questioned about their preferred format for a coping skills intervention, 5% selected the group format, 56% selected the one-on-one format, and 39% selected the self-directed format. Interestingly, more men chose the self-directed format. Beatty et al. [42] recently found support for the efficacy of a self-directed, coping skills workbook for women with breast cancer in improving post-traumatic stress disorder symptoms, cognitive avoidance, and helplessness/hopelessness. The workbook contained information on common medical and psychosocial issues, cognitive behaviour therapy-based worksheets to enable active engagement and processing of these issues, and survivors’ stories. Interestingly, Krischer, Xu & Jacobsen [44] examined the efficacy of a self-administered stress management training intervention among individuals undergoing radiotherapy, including men diagnosed with prostate cancer, and found that distressed individuals benefited more from the self-administered intervention (improvements in mental health and decreased depressive symptoms) than non-distressed individuals. In another context, Dalal et al. [45] found that a self-directed manual was as effective as hospital-based rehabilitation for patients after myocardial infarction in increasing quality of life and reducing total cholesterol levels. The main limitation of the aforementioned self-directed interventions is the exclusive focus on patients, neglecting partners.

Hence, our team has recently developed a self-directed coping skills training intervention for couples affected by cancer, called *Coping-Together,* and this pilot study will examine the feasibility of *Coping-Together* and begin to explore its potential impact on couples’ illness adjustment. For the purpose of the pilot study, the following *Coping-Together* materials will be included: four booklets, a DVD featuring ‘communicating effectively with health care professionals’ and a relaxation audio CD.

## The *Coping-Together* intervention

### Theoretical and empirical underpinnings

*Coping-Together* is a novel, evidence-based, self-directed psychosocial intervention to help couples develop adaptive, individual and dyadic, coping skills and feel more confident in applying these to their current situation. *Coping-Together* builds on three main theoretical frameworks: 1) Lazarus & Folkman’s Stress and Coping framework [46], 2) Bodenmann’s framework of dyadic coping [47], and 3) Bandura’s self-efficacy theory [48].

Of the various coping with stress frameworks, the Lazarus & Folkman framework is the best known and most widely used in the study of stress caused by cancer. This framework explains that the coping process is initiated in response to the individual’s appraisal that important goals have been *harmed, lost, or threatened*[23]. Coping is typically characterised either as problem-focused coping (alter the stressful situation using strategies such as information-seeking, planning and problem-solving) or emotion-focused coping (regulate situation-related emotions using strategies such as positive reappraisal and behavioural disengagement) [23]. These coping styles are often further considered for their adaptive (e.g., positive reappraisal) versus maladaptive (e.g., denial) nature. The assumption is that if individuals use adaptive coping and are able to regain a sense of control over cancer challenges, they are then less likely to experience distress. In this sense, coping is not only a valuable explanatory concept regarding variability in response to stress, it can also serve as a portal for intervention, i.e., when adaptive coping skills are known, they can then be learnt. Although coping strategies may address and resolve the stressor, in some instances, such as a life-threatening illness like cancer, a favourable resolution might not be possible. At this point, the revised Lazarus & Folkman framework [46] proposes that coping then focuses on fostering positive emotions despite the presence of negative feelings engendered by the unresolved stressor. Considerable empirical evidence supports the variables postulated by this framework among individuals diagnosed with cancer and their partners [49-51]. Therefore, this framework provides a strong conceptual basis for *Coping-Together*. *Coping-Together* is expected to provide couples with the resources needed to manage physical and psychosocial cancer challenges that can be addressed directly, whereas for those stressors that cannot be immediately resolved, *Coping-Together* sustains meaning-based coping and fosters positive emotions. How the content of the *Coping-Together* intervention is expected to enhance the coping process is further depicted in Figure 1.

**Figure 1 F1:**
[figure not shown]
**How the *****Coping-Together *****intervention can enhance the coping process.**

Despite the strengths of the Lazarus and Folkman framework, it mainly centers on the individual and the fundamental role that partners play is not explicit. Bodenmann’s framework of dyadic coping [47] extends Lazarus and Folkman’s framework by acknowledging the reciprocal nature of stress and coping within couples. This framework has been most frequently applied within the marital counselling literature, though it is becoming more popular within the cancer literature [52,53]. Broadly speaking, Bodenmann suggests two dyadic coping styles: positive dyadic coping (e.g., supportive communication; joint problem-solving) and negative dyadic coping (e.g., minimising partner concerns; sarcasm, mocking of concerns). Badr and colleagues [52] found that among couples coping with metastatic breast cancer, the use of positive dyadic coping was associated with greater adjustment than the use of negative dyadic coping.

Bandura’s self-efficacy theory posits that people are likely to engage in activities to the extent that they perceive themselves to be competent at those activities [48]. According to Bandura, there are four major sources of self-efficacy: 1) performing a task successfully (mastery experiences), 2) witnessing other people, especially those similar to oneself, successfully complete a task (vicarious experiences), 3) people could be persuaded to believe that they have the skills and capabilities to succeed (e.g., getting verbal encouragement from others to overcome self-doubt), and 4) addressing psychological responses that impact how a person feels about their abilities in a particular situation [54]. To address these sources of self-efficacy, the *Coping-Together* booklets provide step-by-step, practical guides to implement the coping strategies proposed; including behaviour therapy-based worksheets to encourage self-reflection, active learning, and promote application of coping skills to manage challenges confronted and quotes from other patients and partners reporting their success with the proposed coping strategies.

## Content

*Coping-Together* takes on a holistic approach to coping with cancer by including strategies to manage physical, social, psychological, and existential cancer-related challenges. The pilot version of *Coping-Together* includes a series of four booklets developed and qualitatively evaluated by the research team between 2009–2012 [55]. Each booklet addresses one of the following challenges and presents a range of coping strategies shown to be efficacious in managing these: 1) symptom management, 2) couples communicating effectively with health care professionals, 3) supporting each other, and 4) managing worries and emotions. Most available cancer information resources provide information on ‘What is cancer’ and what couples should or need to do, but the *Coping-Together* booklets provide information on ‘*How*’ couples can go about managing cancer challenges [34]. Multiple coping strategies are presented to couples to facilitate a personalised approach, where couples can ‘pick and choose’ and apply those that most closely correspond to their needs. Also, the booklets contain information about additional health care resources. For this pilot, the *Coping-Together* booklets are complemented by electronic media, including a relaxation CD and a 'Communicating effectively with health care professionals’ DVD. Participants will be able to use any or all of these resources at their own discretion and pace prior to collection of the outcome data, which will be 2 months following baseline measurements.

## Study aims and hypotheses

The overall study aims are to 1) examine the acceptability of the methods (e.g., recruitment, survey) to couples affected by prostate cancer and test the feasibility of providing *Coping-Together* and 2) collect preliminary data to investigate the short-term efficacy of *Coping-Together* on couples’ well-being. The study has two arms: 1) *Coping-Together* intervention arm and 2) Minimal ethical care (MEC) arm.

As this is a pilot study, it is not expected that there will be any significant statistical difference between the *Coping-Together* and MEC groups on primary and secondary outcomes; however, it is hypothesised that trends will be noted where *Coping-Together* couples will experience less anxiety (primary hypothesis), cancer specific distress and depression and more positive illness or care giving appraisal, self-efficacy, quality of life (QOL), relationship satisfaction and positive individual and dyadic coping (secondary hypotheses) at 2 months post-baseline compared to MEC couples.

## Methods/design

### Design

The proposed study is a multicentre, stratified, double-blind, two-group, parallel, randomized controlled trial to compare *Coping-Together* to MEC. The design of this study was guided by the Medical Research Council framework for developing and evaluating complex interventions [56] and the CONSORT statement [57].

### Sample

Based on other psycho-oncology feasibility studies [43,58,59] and suggestions by Hertzog [60], 35 couples/group will be recruited for this pilot.

#### Inclusion and exclusion criteria

Men diagnosed in the past 4 months with a primary, early-stage, prostate cancer, receiving or planning to receive treatment (including active surveillance), and their partner (spouse, boy/girlfriend, or de facto) will be invited to participate in the study. Additional inclusion criteria will be either the patient or their partner is identified by the Distress Thermometer (DT) as distressed (i.e., patient score of four or more) at the time of recruitment [36] and both need to be sufficiently fluent in English and cognitively able to complete surveys. Patient and partner consents are required for the couple to participate in this trial. As *Coping-Together* was designed to bring about change in how couples’ cope with cancer challenges and decrease anxiety, couples will be targeted soon after diagnosis, a time typically marked by many concerns and needs [61,62]. Moreover, as it is now well-recognised that ignoring patients’ or partners’ baseline distress can undermine the efficacy of an intervention (given the potential for floor effect) [63], distressed patients or partners are included in this study.

### Procedures

It is anticipated that most eligible men will be recruited through urologists’ private practices in Australia (New South Wales and South Australia). Weekly, urologists will identify patients meeting the medical (recent, primary, early-stage prostate cancer diagnosis and receiving/planning to receive treatment) and English fluency inclusion criteria. At their next appointment, interested patients will be invited to meet with the on-site research assistant to further discuss study participation and obtain a score on the DT. The research assistant will give interested and eligible participants a study package, which includes an information statement, a consent form, baseline survey, and a study pack to pass on to their partner. The team will follow-up one to two weeks later with non-responders. If the on-site research assistant is not present in the clinic, the urologists will give interested patients a study pamphlet and obtained verbal consent for a member of the team to contact them within the following week. The study will also be advertised through a range of media outlets, including radio, print, and online channels. It is anticipated that 370 patients will be approached to recruit the target sample size, assuming that 35% of patients or partners score four or more on the DT [64]; of those, 25% of couples will be ineligible, 30% will refuse participation, and 7% will be lost to follow-up [65]. This study has been approved by the University of Newcastle and the University New South Wales Human Research Ethics Committees.

### Randomization of group assignment

A computer-generated, randomization schedule with block lengths of variable size (4 and 6 couples) and stratified by recruitment source will be accessible to the main research assistant to allow assignment of a unique study ID to each couple as their consent forms/baseline surveys are received. Block randomisation is used to achieve balance in the allocation of couples across the MEC and *Coping-Together* groups and varying the block size reduces the chance of treatment allocation being known [66].

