### Blinding

Participants will be told they will receive one of two information packs, but as they do not know which one is the study intervention and the study survey and contact with the research team is comparable across groups, they are blinded to whether they are in the MEC or *Coping-Together* group. The participants will also be blinded to study hypotheses. As it is expected that couples will mainly use *Coping-Together* at home, the chance of MEC participants being exposed to the intervention is minimal.

All contact with the couples will occur through the same research assistant(s) who will not be blinded to group allocation and will assign a study ID, randomise participants, send study packs, and conduct follow-up phone calls. A separate research assistant, who will have no contact with participants and will be blinded to group allocation, will enter the data. The chief investigators and the statistician will not be able to link study IDs (and surveys) back to a recruitment site or group and are therefore blinded to group allocation.

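### The unblinded research assistant role that handles couples also has access to the randomisation schedule; no independent list holder or one-at-a-time release is described, and varying block sizes do not protect against a list reader

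*Protocol article*

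**What the plan says.** The protocol article covers allocation in three places.

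- **Randomization of group assignment.** The list is described as "A computer-generated, randomization schedule with block lengths of variable size (4 and 6 couples) and stratified by recruitment source". It "will be accessible to the main research assistant to allow assignment of a unique study ID to each couple as their consent forms/baseline surveys are" returned. The reason given for mixing block lengths is that "varying the block size reduces the chance of treatment allocation being known".
- **Blinding.** "All contact with the couples will occur through the same research assistant(s) who will not be blinded to group allocation". These same people "will assign a study ID, randomise participants, send study packs, and conduct follow-up phone calls". The investigators, the statistician and a separate data-entry assistant are the ones kept unaware of group.
- **Procedures.** Before allocation, "interested patients will be invited to meet with the on-site research assistant to further discuss study participation and obtain a score on the DT". Afterwards, "The team will follow-up one to two weeks later with non-responders".

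The only safeguard named for the sequence itself is the varying block size. The article mentions no list holder outside the recruiting staff, no central release and no sealed assignments.

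**The concern.** Concealing upcoming allocations is a separate matter from blinding after allocation. It ensures that the decision to enrol a couple, and the moment at which they are enrolled, cannot depend on the arm they would enter. Here the text places access to the list, contact with couples and the act of randomising in one unblinded role.

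The planned ANCOVA adjusts for the participant's baseline score. It cannot remove differences in traits that are not in the model, such as willingness to work through self-help material, if those influenced who entered which arm. Being a pilot does not make this harmless. The second aim is preliminary evidence on short-term efficacy, the Implications section says the results will be used to design a larger trial, and the first aim is to test the trial methods, of which allocation is one.

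**Working it through.** The plan states no figure on this point, so there is none to reproduce. The check is a comparison of sections, followed by a small calculation of what varying the block size achieves.

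**Step 1: who can see the list, and who deals with couples**

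| Function | Who, according to the article | Section |
|---|---|---|
| Access to the schedule, assigning IDs | Main research assistant | Randomization of group assignment |
| All contact, IDs, randomising, mailing, calls | The same research assistant(s), unblinded | Blinding |
| Discussing participation, obtaining the DT score, handing out packs | On-site research assistant | Procedures |
| Following up non-responders | The team | Procedures |

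The first two rows overlap directly, since both assign the ID. The Blinding section then gives all contact to that same role. Read as written, contact before randomisation is included.

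**Step 2: what timing protects and what it does not**

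Assignment happens once the couple's forms have come in, so knowledge of group cannot colour their baseline answers. Three activities come earlier and remain exposed if the person doing them can read the list: the discussion of participation, the follow-up of non-responders, and the order in which returned forms from one recruitment source are processed.

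**Step 3: what varying the block size achieves**

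Inputs from the article: blocks of 4 and 6, two equal groups, 70 couples. Assumptions: a single stratum, block sizes 4 and 6 equally likely (the mix is not stated), and an observer who makes the best guess from past allocations.

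For a known block of length 2m:
- expected correct guesses = m + (2^(2m)/C(2m,m) − 1)/2 (Blackwell–Hodges)
- expected fully determined assignments = 2m/(m+1)

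Blocks of 4 (m = 2):
- 2 + (16/6 − 1)/2 = 2.833, and 2.833/4 = 70.8% correct
- 4/3 = 1.333, and 1.333/4 = 33% fully determined

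Blocks of 6 (m = 3):
- 3 + (64/20 − 1)/2 = 4.1, and 4.1/6 = 68.3% correct
- 6/4 = 1.5, and 1.5/6 = 25% fully determined

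Mixed 4 and 6, current size unknown (20,000 simulated sequences of 70 couples): 69.0% correct, 5.6% certain.

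| Observer | Guessed correctly | Certain |
|---|---|---|
| Past allocations, known blocks of 4 | 70.8% | 33% |
| Past allocations, known blocks of 6 | 68.3% | 25% |
| Past allocations, mixed 4 and 6 | 69.0% | 5.6% |
| Anyone who can read ahead on the list | 100% | 100% |

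Mixing the blocks therefore cuts certain knowledge substantially for someone without the list. For someone who can read ahead on it, block size makes no difference.

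**The case against.** Several points on the other side carry weight.

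- **Accessible is not the same as fully visible.** A reader might infer that the whole list lies open and that every coming allocation is known. The article does not say so. It says the schedule is accessible for assigning IDs, and a journal article may leave release details to a fuller protocol. What stands is that the article does say who has access, and the one safeguard it names does not work against that person.
- **Main and on-site assistants may be different people.** The trial is multicentre and the two labels differ, so the person screening a given patient may not hold the list. But the Blinding section gives all contact and randomisation to the same role. If a separation is intended, the text should say so.
- **The room for steering is limited.** Urologists identify patients on the medical and language criteria. The DT score is a number the patient circles, with a fixed cut-off of four. Couples decide whether and when to return their forms, and processing order matters only when forms from one source are on hand together. All of this reduces the risk without removing it.
- **The block-size sentence is not wrong in general.** A reader might call the protection void. Step 3 shows that it does help against staff who know only past allocations.
- **A figure for the bias is tempting.** It would need the number of couples steered and how they differ in outcome after baseline adjustment. The documents give neither, so any figure would be invented.

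**Conclusion.** The concern holds in a limited form. The article gives an unblinded research assistant access to the randomisation schedule, gives the same role all contact with couples and the task of randomising them, and describes no independent holder or stepwise release. Concealment is therefore not secured by what is written, and varying block lengths cannot supply it against a person who can read the list.

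This rests on reading the two assistant descriptions together, as the Blinding section invites, and on the absence of any described release mechanism. The article does not show that steering would occur or that every allocation would be foreseen. The percentages in Step 3 measure predictability under the stated assumptions; they are not a measure of bias, whose size stays unknown. The matter should be settled before couples are randomised, because selection at entry cannot be undone in the analysis.

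**What to change.** Amend Randomization of group assignment and Blinding so that nobody who recruits, screens or follows up couples can see upcoming allocations.

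- Use a password-protected allocation program, or sequentially numbered opaque sealed envelopes for each recruitment source.
- Have the sequence prepared by someone who does not deal with participants. The statistician, the investigators and the data-entry assistant are meant to stay blinded, so a one-off preparer outside those roles is simplest.
- Release one allocation at a time, only after the couple's consents and baseline surveys are logged with date and time.
- State whether the main and on-site research assistants are the same people.

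The assistant may still learn each allocation after release in order to mail packs and make calls. Past allocations then remain known to that person. Under the Step 3 assumptions this leaves about 69% of next assignments guessable and about 6% certain, and this is where varying the block size is useful.

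The cost is a short amendment and a small set-up effort. No further trial staff are needed and nothing is added for couples.
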